## 9 STATISTICAL CONSIDERATIONS

The statistical methods and analysis will be described in detail in the statistical plan.

The primary endpoint is the area under each subject's artesunate (ARS) concentration-time curve (AUC). Secondary endpoints are a) the maximum concentration ( $C_{max}$ ), time to reach maximum concentration ( $T_{max}$ ), and half life ( $t_{1/2}$ ) for ARS, and b) the above four parameters for DHA.

The null hypothesis for each comparison is that the mean value of the endpoint does not differ between control and intervention arms. The alternative hypothesis is that the mean values of each endpoint do differ between control and intervention. Each alternative hypothesis is two-sided (ie intended to detect superiority or inferiority).

To be included in the analysis, a subject must have missed at most one of the follow-up times. Any subject in either intervention arm who did not receive all two doses of charcoal will not be included in the analysis. Any subject in the control arm who received one or more doses of charcoal will not be included in the analysis.

Following Nealon et al.(14), both one- and two-compartment models will be used for both ARS and DHA, and the better fit model will be used. The packages nlmeODE, odesolve and nlme be used with the R software (23).

Primary analysis will be by one way ANOVA on the log-transformed values of AUC and other pharmacokinetic variables. Each intervention arm will be compared to control by a contrast. If the untransformed variables have a distribution closer to normal than the log-transformed ones, then a secondary analysis will be ANOVA on the untransformed variables.

To achieve 80% power to detect a ratio of means of 1.5 of mean AUC, or other pharmacokinetic parameter, between control and either intervention arm, with coefficient of variation of 50% and two-sided significance level of 5%, we will need 23 subjects per arm (Table 2 of van Belle and Martin, 1993, American Statistician, 47: 165-167). With 30 subjects per arm, we will achieve this sample size if 20% are lost to follow-up or otherwise ineligible for inclusion in the analysis.

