In general, enhanced clearance of a drug upon co-administration of charcoal can be expected if the drug has a small volume of distribution (Vd), low binding affinity for plasma proteins, and a low endogenous clearance (Cl) (12).

Apart from quinine, artesunate, a water soluble artemisinin derivative that has a low Vd (0.15l/kg), but a high clearance rate of 50ml/kg/min can be used to treat severe malaria.

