## Clinical Trial: Charcoal

In South East Asia a randomized controlled multi center trial revealed that parenteral artesunate is superior to i.v. quinine for the treatment of severe malaria, reducing the mortality from 22% (quinine) to 15% (artesunate) (13). The planned AQUAMAT trial will evaluate this approach in several African sites including the Gambia, where it is conducted by the MRC unit's malaria programme.

Artesunate undergoes rapid biotransformation in the liver that yields the metabolite dihydroartemisinin (DHA) to which the beneficial antimalarial effect of artesunate is ascribed. A literature search performed by [name] and [name] has revealed that calculated pharmacological parameters do vary between settings, age of the subject and severity of disease (14-16) To design the sampling strategy an estimate of the half-life and  $T_{max}$  of artesunate after i.v. administration has been constructed based on data derived from healthy volunteers (see table 1 below).

**Table 1: Reported half life ( $t_{1/2}$ ) and time to reach maximum concentration ( $t_{max}$ ) for artesunate and its active metabolite after i.v. administration**

| DRUG                | $t_{1/2}$ [min]  | Clearance [L/hr/kg] |
|---------------------|------------------|---------------------|
| i.v. artesunate     | 3.1 ( $\pm$ 1.1) | 2.8 ( $\pm$ 0.4)    |
| Dihydroartemisinin* | 47 ( $\pm$ 14.8) | 1.3 ( $\pm$ 0.6)    |

\*Artesunate is readily hydrolyzed to dihydroartemisinin, probably by blood esterases and the hepatic cytochrome P450 3A4.

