**Clinical Trial: Charcoal**

---

and have an excellent safety record, we believe it is ethical to perform these trials in patients of this age group. In order to obtain meaningful results with regard to the planned efficacy trial in severely ill children, we aim to administer artesunate intravenously. This initial study is to demonstrate if oral AC impacts on the pharmacokinetics of i.v. artesunate.

Due to the extremely short half life of i.v. artesunate, the minimal sample size required per group is 30, thus a total of 90 subjects need to be enrolled. Subjects will be randomised and enrolled into one of the following groups:

- 1) artesunate i.v. without adjuvant treatment (control group) 350ml water given orally with each i.v. dose
- 2) artesunate i.v. and oral charcoal (50g) given simultaneously with each dose of artesunate
- 3) artesunate i.v. followed by oral charcoal (50g) given 1 hour after each dose of artesunate

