### 3 TRIAL OBJECTIVES

#### 3.1 Trial Objectives

The primary objective is to evaluate whether orally given AC alters the pharmacokinetic of intravenously applied artesunate and its metabolite dihydroartemisinin (DHA) when given simultaneously or after 1 hour.

The general purpose is to study the pharmacokinetic interactions between artesunate and AC as part of a “proof of principle” studies for the use of AC as an adjuvant treatment in mild and severe malaria in African children.

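### Artesunate AUC, the sole primary endpoint, cannot detect an effect of charcoal given 1 hour after the sampled dose; DHA, named in the primary objective, is only secondary

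*Protocol*

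**What the plan says.** Section 9 of the protocol fixes one primary endpoint: "The primary endpoint is the area under each subject's artesunate (ARS) concentration-time curve (AUC". The remaining artesunate parameters are secondary, as are "b) the above four parameters for DHA". Each charcoal arm is compared with control by a contrast in a one-way ANOVA on log values. The sample size of 23 per arm (30 enrolled) is stated to give 80% power for a ratio of 1.5 between control and either charcoal arm.

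Section 2.2 describes Group 3 as "artesunate i.v. followed by oral charcoal (50g) given 1 hour after each dose of artesunate". Appendix A puts these charcoal doses at 1 h and 13 h. Sections 3.2 and 7.2.2 place all drug-level samples after the second artesunate dose at 12 h, from 5 min to 6 h.

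Section 3.1 asks whether charcoal "alters the pharmacokinetic of intravenously applied artesunate and its metabolite dihydroartemisinin (DHA) when given simultaneously or after 1 hour". The objective in the Protocol Summary and the aim in Section 2.2 name artesunate only. Section 2.1 refers to "dihydroartemisinin (DHA) to which the beneficial antimalarial effect of artesunate is ascribed", and Table 1 there gives half-lives of 3.1 (±1.1) min for artesunate and 47 (±14.8) min for DHA.

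**The concern.** Artesunate disappears within minutes, while Group 3 takes its charcoal an hour later. If the artesunate AUC is complete by then, the headline test for one of the two charcoal arms says nothing about the timing that defines that arm. A null result could be read as reassurance that charcoal given an hour after artesunate leaves the active drug alone, when the endpoint could not have shown otherwise. The moiety that could show it is DHA. It is part of the Section 3.1 objective and is credited with the antimalarial effect, but it sits below the primary endpoint.

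**Working it through.** **1. The plan's sample size.** Inputs from Section 9: ratio 1.5, CV 50%, two-sided 5%, power 80%.
- Log SD = √ln(1 + 0.5²) = 0.472; ln 1.5 = 0.405.
- n = 2 × [0.472 × (1.960 + 0.842) / 0.405]² = 21.3, so 22 per arm by the normal approximation.
- With the noncentral t for two groups, power is 79.4% at 22 and 81.2% at 23.
- 30 × 0.8 = 24, which covers 23.

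The figure of 23 reproduces. The question is what it applies to.

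**2. Artesunate AUC left when Group 3 takes charcoal.** For an intravenous bolus with mono-exponential decline, the share of AUC still to come at time T is 2^(−T/t½).

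| Half-life | Gap | Share left |
|---|---|---|
| 3.1 min (Table 1) | 60 min | 2^(−19.4) = 0.0000015 |
| 4.2 min (mean + 1 SD) | 60 min | 0.00005 |
| 5.3 min (mean + 2 SD) | 60 min | 0.0004 |
| 5.3 min | 50 min | 0.0014 |

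The ± values are read as SDs. The 50 min gap arises if both ±5 min windows in Appendix A run against each other. Section 2.1 says artesunate "has a low Vd (0.15l/kg), but a high clearance rate of 50ml/kg/min", which implies a shorter half-life still: 0.693 × 0.15 / 0.050 = 2.1 min.

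In the last row, removing everything that remained would give an AUC ratio of 1 / (1 − 0.0014) = 1.0014. Power for that is 5.0% at 23 or 30 per arm, which is the significance level itself.

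**3. What the contrast can still reflect.** Group 3's first charcoal dose is at 1 h and the sampled artesunate dose is at 12 h. Charcoal still present 11 hours on could act on the sampled artesunate. The protocol gives no figure for this.

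**4. DHA AUC left at 1 hour.** Assume first-order formation at ka = ln 2 / 3.1 = 0.2236 per min and elimination at ke = ln 2 / 47 = 0.01475 per min. The share of AUC after time T is (ka·e^(−ke·T) − ke·e^(−ka·T)) / (ka − ke).
- T = 60 min: 0.442. With DHA half-lives of 32.2 and 61.8 min (±1 SD) it is 0.304 and 0.537.
- A ratio of 1.5 means a fall to 2/3 of control. This needs a cut in post-1-hour exposure of 0.333 / 0.442 = 75%. At a half-life of 32.2 min it is out of reach, since complete removal gives only 1 / (1 − 0.304) = 1.44.
- A one-third cut after 1 hour (illustrative) gives a total-AUC ratio of 1 − 0.442 / 3 = 0.853.

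**5. Power for that one-third cut.** Noncentral t with three-group ANOVA degrees of freedom, at 23 and 30 per arm.

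| Metric | Ratio | CV | Power |
|---|---|---|---|
| Total DHA AUC | 0.853 | 50% | 20%, 25% |
| DHA AUC 1–6 h | 0.667 | 50% | 82%, 91% |
| DHA AUC 1–6 h | 0.667 | 55% | 75%, 86% |
| DHA AUC 1–6 h | 0.667 | 72% | 55%, 67% |

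The CV of the 1–6 h AUC is not in the protocol. It depends on half-life as well as clearance. Treating the Table 1 values as independent gives about 55%; letting half-life changes pass through to clearance gives about 72%. If charcoal took 30 min to act (illustrative), the cut would fall on only (0.284 − 0.005) / (0.442 − 0.005) = 64% of the 1–6 h AUC. The ratio would then be 1 − 0.64 / 3 = 0.79, with power of about 39% and 49% even at CV 50%.

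**The case against.** A reader might infer that the Group 3 primary contrast is null by construction. The documents do not support that. Group 3 has already taken charcoal 11 hours before the sampled dose, and a carry-over effect would show in this contrast. Section 2.1 expects charcoal to enhance clearance "if the drug has a small volume of distribution (Vd), low binding affinity for plasma proteins, and a low endogenous clearance (Cl", and calls artesunate's clearance high. That makes a large carry-over effect unlikely, but it is an expectation about the drug and not a consequence of the design.

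Nor does it follow that the trial cannot answer its objective for Group 3. DHA is sampled at every time point, its four parameters are pre-specified, and Section 9 applies the same ANOVA and contrasts to them. The power statement also extends to other pharmacokinetic parameters. The DHA question is ranked lower, not lost. The protocol likewise has no rule tying later efficacy trials to artesunate AUC; Section 15 refers to the trial's data as a whole.

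The endpoint does fit the objective in the Protocol Summary and the aim in Section 2.2, which name artesunate alone. So part of the defect is that the objectives disagree among themselves.

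Finally, a separate primary metric for each charcoal arm would not sit easily in a single one-way ANOVA. The 60 min sample also coincides with Group 3's charcoal dose, which leaves only three samples after it, and Section 9 tolerates one missed sample. These points count against making the 1–6 h AUC primary. They do not touch the finding on artesunate AUC.

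**Conclusion.** The concern holds in a limited form. On the protocol's own half-life, over 99.8% of artesunate AUC has accrued before Group 3 takes charcoal after the sampled dose, even under unfavourable inputs. The Group 3 primary contrast is uninformative about that dose; any effect that it shows would be carry-over from about 11 hours before sampling began. The 80% power stated for either arm does not apply to the 1-hour question.

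The artesunate conclusion rests on Table 1 and mono-exponential decline, and has a wide margin. The DHA figures are softer: they assume first-order kinetics, ± as SD, an assumed CV and an immediate charcoal effect. They show that DHA can carry the question, but with less power for Group 3 than Section 9 suggests.

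**What to change.** In Section 9:

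- Make DHA AUC after the second dose the primary endpoint, or co-primary with artesunate AUC under a stated multiplicity rule.
- State that the Group 3 artesunate AUC contrast reflects only carry-over from the first charcoal dose and is not evidence about charcoal given at 1 hour.
- Add DHA AUC from 1 to 6 h as a pre-specified supportive analysis for Group 3, using the 60 min, 90 min, 3 h and 6 h samples already scheduled.
- Restate the Group 3 power for total DHA AUC and re-justify the ratio of 1.5. Give power for the 1–6 h AUC over a range of CVs and allow for a lag in charcoal's effect.

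Reconcile the objectives in the Protocol Summary and Section 2.2 with Section 3.1, so that all say whether DHA is included.

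The cost is wording in the protocol and the statistical plan, with no new samples, assays or subjects. The downsides are small: a multiplicity rule if the endpoints are co-primary, and a less favourable stated power for Group 3.

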**Plasma level determination**

Plasma samples will be collected to determine the levels of artesunate and its metabolite DHA as well as para-aminobenzoic acid (PABA) at the time points 5, 10, 15, 30, 60, 90 min and 3 and 6 hours after the second dose of artesunate has been given. Samples will be frozen immediately and stored in LiN2 at the MRC field station nearby, and will be transported on dry ice via Fajara to the London School of Hygiene and Tropical Medicine in the UK. Here, samples will be analyzed by liquid chromatography – mass spectrometry (LC-MS)

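### One missed-sample rule for both analytes removes subjects from the primary artesunate AUC analysis over samples, and a charcoal dose, that come too late to affect it

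*Protocol*

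**What the plan says.** Protocol Section 9 makes the AUC of artesunate the primary endpoint. The secondary endpoints are three further artesunate parameters and "the above four parameters for DHA". Samples for both analytes are taken "at the time points 5, 10, 15, 30, 60, 90 min and 3 and 6 hours after the second dose of artesunate has been given" (Section 7.2.2, Plasma level determination).

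Inclusion is governed by a count: "To be included in the analysis, a subject must have missed at most one of the follow-up times". The rule covers the analysis as a whole. It does not separate artesunate from DHA, or early samples from late ones.

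A second rule concerns charcoal: "Any subject in either intervention arm who did not receive all two doses of charcoal will not be included in the analysis". The next sentence excludes any control who was given charcoal. Appendix A places the second charcoal dose of group 3 at 13 h, which is 60 min after the second artesunate dose.

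The AUC is to come from compartment models: "both one- and two-compartment models will be used for both ARS and DHA, and the better fit model will be used". The software named is nonlinear mixed-effects software (nlme, nlmeODE). Section 5.3 says that dropouts are not replaced.

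**The concern.** The eight samples are far from equally informative about artesunate. Table 1 (Section 2.1) gives it a half-life of 3.1 min, against 47 min for DHA. A count that treats all eight alike works against the primary endpoint in two ways. It discards subjects whose missing samples hold no artesunate information. It also keeps, without comment, subjects who lack the most informative artesunate sample.

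The charcoal rule has a similar effect in group 3. A subject who takes the first charcoal dose but misses the one at 13 h leaves the artesunate analysis, although that dose falls after nearly all of the artesunate has gone.

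At stake are the precision of the primary comparison and the part of the 20% loss allowance that such exclusions use up. All of them are made after randomisation, and failure to finish the charcoal can occur only in the two charcoal arms.

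**Working it through.** **The plan's sample size.** Inputs from Section 9: ratio of means 1.5, CV 50%, two-sided 5%, 80% power.
- Log-scale SD = √ln(1 + 0.5²) = 0.472. Then n = 2 × (1.960 + 0.842)² × 0.472² / (ln 1.5)² = 21.3, so 22 per arm. Taking the CV directly as the log SD (0.5) gives 23.9, so 24. The stated 23 lies between them and is reproduced.
- 30 × 0.8 = 24, which covers 23.
- Noncentral-t power for one contrast, with variance pooled over three arms (SD 0.472): 83.4% at 24 per arm, 81.8% at 23, 80.0% at 22, 78.1% at 21.

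**Where the artesunate AUC lies.** The assumption is mono-exponential decay after the i.v. dose. The share of AUC after time t is then 2^(−t / t½). The range uses Table 1's half-life ± 1.1 min. As a cross-check, Section 2.1 says artesunate "has a low Vd (0.15l/kg), but a high clearance rate of 50ml/kg/min", which implies t½ = 0.693 × 0.15 / 0.05 = 2.1 min, inside that range.

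| Share of artesunate AUC | t½ 3.1 min | t½ 4.2 min | t½ 2.0 min |
|---|---|---|---|
| before 5 min | 67% | 56% | 82% |
| before 10 min | 89% | 81% | 97% |
| after 30 min | 0.12% | 0.7% | 0.003% |
| after 60 min | 1.5 × 10⁻⁶ | 5 × 10⁻⁵ | 9 × 10⁻¹⁰ |
| after 90 min | 1.8 × 10⁻⁹ | 3.5 × 10⁻⁷ | 3 × 10⁻¹⁴ |

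**Subjects dropped.** Two misses exclude a subject, and there are 8 × 7 / 2 = 28 possible pairs. Of these, 4 × 3 / 2 = 6 fall wholly among 60 min, 90 min, 3 h and 6 h. If 3 h and 6 h are missed, the AUC beyond the last remaining sample (90 min) is about 2 × 10⁻⁹ of the total.

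**Subjects kept.** If only 5 min is missed, the share before the first value rises from 67% to 89%. The effect on precision was simulated by fitting a log-linear decline to each simulated subject. The residual CV of 15% is an assumption, since the protocol gives none. SD of the estimated log AUC at t½ 3.1 min:
- 5, 10, 15, 30 min: 0.11
- 5, 10, 15 min: 0.14
- 10, 15, 30 min: 0.16
- 10 and 15 min only: 0.35 (0.19 to 0.55 over residual CV 10–20% and t½ 2.0–4.2 min)

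The last case arises if 5 min is missed and 30 min cannot be quantified. The level at 30 min is about 0.1% of the starting level, and the protocol states no assay limit. Combined with the between-subject SD of 0.472, the total SD is √(0.472² + 0.11²) = 0.49 for the four early samples, 0.50 for 10, 15 and 30 min, and 0.59 for 10 and 15 min only.

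**The 13 h charcoal dose.** At 60 min after the second artesunate dose, 1.5 × 10⁻⁶ of the artesunate AUC remains (at most 5 × 10⁻⁵). Missing that dose cannot noticeably change the primary endpoint.

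**DHA.** With half-life 47 min (32.2 to 61.8) and simple decay, 41% (28–51%) of the AUC lies after 60 min, 26% (14–36%) after 90 min and 7% (2–13%) after 3 h. Late samples and the 13 h dose do matter here.

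**The case against.** The best defence is that one analysis set serves both analytes. The primary objective (Section 3.1) names DHA as well as artesunate, and a good part of the DHA curve lies late. This stands as a reason for a late-sample rule for DHA. It gives no reason to apply that rule to artesunate.

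The practical effect may also be small. Subjects are inpatients with an indwelling catheter, the protocol gives no missed-sample rate, and power is still 80.0% at 22 per arm, so eight of 30 can be lost. This stands too, and limits the size of the point.

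A reader might go further in three ways that the documents do not support.
- **That without the 5 min sample the AUC cannot be estimated.** The 10, 15 and 30 min samples remain, and a mixed-effects fit also borrows from other subjects. With those three samples the total SD rises by only about 3% (0.50 against 0.49).
- **That the excluded subject's AUC is fully determined.** Even with all eight samples, 67% of it precedes the first value. It is only as well determined as in a complete subject.
- **That the charcoal rule is one-sided and biases the contrast.** Section 9 has a mirror exclusion for controls given charcoal. Exclusions will probably fall mainly on the charcoal arms, but no arm-specific rate is given and no bias is shown. Analysing subjects who took the charcoal is also a reasonable primary set for an interaction question.

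Section 9 leaves detail to a statistical plan that is not at hand. The absence of an as-randomised run from the protocol is therefore not counted as a fault. The stated rules are.

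**Conclusion.** The point holds as a mismatch between a stated inclusion rule and the primary endpoint. Subjects who miss two samples from 60 min on, and group 3 subjects who miss only the 13 h charcoal dose, are removed from the artesunate analysis although at most about 5 × 10⁻⁵ of the AUC is involved. Subjects who miss only the 5 min sample are kept with a less precise and more model-dependent estimate. That loss is slight if 30 min is quantifiable and material if it is not.

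The harm is lost precision: around 24 per arm, each evaluable subject lost from every arm costs about 1.6 to 1.8 points of power. The sample size itself is not in question.

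The conclusion rests on Table 1's half-life and mono-exponential decay. A slow second phase for artesunate, which the planned two-compartment fit would allow, would give late samples more weight, but the protocol reports none. The precision figures also rest on the assumed residual CV.

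**What to change.** Replace the single count in Section 9 with a rule per analyte.
- **Artesunate AUC:** judge only the samples up to 30 min, with a stated minimum number of quantifiable ones, and ignore misses from 60 min on. Three is a natural candidate, since the two sets of three shown above give 0.14 and 0.16. Making the 5 min sample compulsory is not supported, because 10, 15 and 30 min do almost as well as 5, 10 and 15 min. Quantifiability depends on exposure, so count values below the assay limit by arm and keep them apart from samples not taken.
- **DHA:** require stated late-sample coverage.
- **Charcoal:** keep the charcoal-completion set for the primary contrast if wanted. Add the same ANOVA on all randomised subjects with both artesunate doses and an evaluable AUC, including group 3 subjects who missed only the 13 h charcoal dose. Report exclusions by arm and reason.

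The cost is a few sentences and one extra run. The artesunate and DHA sets may differ slightly. Sample size, sampling times and treatment are unchanged.

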### 5.3 Withdrawal of Subjects

Subjects may withdraw voluntarily from participation in the study at any time. Subjects may also withdraw voluntarily from receiving the study intervention for any reason. Subjects who dropped out for any reason will not be replaced.

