| 12h 15 min*
(Time point 5)        | 
 
- Serum Creatinine, Albumin.
 
- Plasma Artesunate, DHA
 
                                                                                                                                                               |
| 12h 30 min*
(Time point 6)        | 
 
- Serum Creatinine, Albumin.
 
- Plasma Artesunate, DHA
 
                                                                                                                                                               |
| 13h ± 5min*
(Time point 7)        | 
 
- Serum Creatinine, Albumin.
 
- Plasma Artesunate, DHA
 
- AC to subjects in group 3 only
 
                                                                                                                     |
| 13h 30 min ± 5min*
(Time point 8) | 
 
- Serum Creatinine, Albumin.
 
- Plasma Artesunate, DHA
 
                                                                                                                                                               |
| 15h ± 5min*
(Time point 9)        | 
 
- Serum Creatinine, Albumin.
 
- Plasma Artesunate, DHA
 
                                                                                                                                                               |
| 18h ± 5min*
(Time point 10)       | 
 
- Full biochemistry
 
- Plasma Artesunate, DHA
 
                                                                                                                                                                        |
| 18h 5min – 24hrs                      | 
 
- Clinical assessment by qualified physician
 
- Discharge
 
                                                                                                                                                            |

\* All time points measured from the time of the first dose of IV artesunate.

For details see Section 7.

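### Section 9 drops Group 3 subjects from the primary artesunate AUC analysis for missing a charcoal drink that falls due after that AUC has accrued

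*Protocol*

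**What the plan says.** Section 9 makes the AUC of artesunate the primary endpoint. C_max, T_max and half-life of artesunate are secondary, as are the same four parameters for DHA. Three inclusion rules then apply to the analysis as a whole, with no distinction by endpoint:

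- All arms: "To be included in the analysis, a subject must have missed at most one of the follow-up times."
- Charcoal arms: "Any subject in either intervention arm who did not receive all two doses of charcoal will not be included in the analysis."
- Control: "Any subject in the control arm who received one or more doses of charcoal will not be included in the analysis."

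Section 2.2 describes Group 3 as "artesunate i.v. followed by oral charcoal (50g) given 1 hour after each dose of artesunate". Control has "350ml water given orally with each i.v. dose", and no rule requires that the water was drunk. Appendix A puts the second artesunate dose at 12 h and, at 13 h, "AC to subjects in group 3 only". Plasma is sampled only after the second artesunate dose, from 5 min to 6 h.

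Section 5.3 separates leaving the study from declining treatment: "Subjects may also withdraw voluntarily from receiving the study intervention for any reason." It also says that dropouts are not replaced.

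**The concern.** A completion rule makes sense where the missed dose could have changed the measurement. For Group 3 and the primary endpoint, the second drink comes after the event of interest. Artesunate disappears within minutes, so the curve that defines the primary endpoint is in effect finished when the drink is offered. Someone who declines it but stays for blood sampling has an intact primary-endpoint profile and is still deleted.

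Two things are at stake. Usable randomised profiles are lost for no gain in validity. The deletion also follows randomisation, in an open-label trial, and occurs after the exposure that is being measured, so it could in principle depend on that exposure. Control has no comparable filter: it can lose subjects for receiving charcoal or for missed samples, but not for failing to complete its drink.

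**Working it through.** **Inputs.** Artesunate half-life 3.1 (±1.1) min and DHA half-life 47 (±14.8) min (Section 2.1, Table 1). Second artesunate dose at 12 h and Group 3's second drink at 13 h, each ±5 min (Appendix A). CV 50%, ratio 1.5, two-sided 5%, 80% power, 23 per arm needed and 30 enrolled (Section 9).

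**The plan's own figure.** SD of log AUC = √ln(1 + 0.5²) = 0.472; difference = ln 1.5 = 0.405. The normal approximation gives 2 × [0.472 × (1.960 + 0.842)/0.405]² ≈ 21.3, so 22 per arm. With the noncentral t, power is 79.4% at 22 and 81.2% at 23. The stated 23 is reproduced, and 30 × 0.8 = 24 covers it.

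**Artesunate AUC still to come at 60 min.** For a one-compartment i.v. bolus the remaining fraction is 2^(−60/t½):

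- mean, 3.1 min: 1.5 × 10⁻⁶ (0.00015%)
- mean + 1 SD, 4.2 min: 5.0 × 10⁻⁵ (0.005%)
- mean + 2 SD, 5.3 min: 3.9 × 10⁻⁴ (0.04%)
- mean + 3 SD, 6.4 min: 1.5 × 10⁻³ (0.15%)

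At least 99.8% has accrued in every case. If the ±5 min windows leave only 50 min between artesunate and charcoal, the figure at 6.4 min is 2^(−50/6.4) = 0.45%, which changes nothing.

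**DHA AUC still to come at 60 min.** In a one-compartment parent-to-metabolite model with k_p = ln 2/3.1 and k_m = ln 2/47, the fraction is k_p/(k_p − k_m) × [e^(−60k_m) − (k_m/k_p)e^(−60k_p)] ≈ 1.071 × 0.413 = 0.44. With both half-lives about 1 SD lower or higher it is 29% to 55%. For DHA the 13 h drink can matter.

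**Who is reached.** A Group 3 subject who leaves at 13 h misses the 90 min, 3 h and 6 h samples and is already excluded by the missed-sample rule. The point concerns those who decline only the second drink and stay for sampling, which Section 5.3 permits.

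**Possible selection (assumptions, not in the protocol).** Suppose that one charcoal arm loses a fraction p in one tail of a trait that has correlation r with log AUC. The false shift is r × 0.472 × φ(z_p)/(1 − p), where φ(z_p) is the normal density at the cut-off. For r = 0.2 to 0.5:

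- p = 10%: false ratio 1.02 to 1.05 (or its inverse), type I error 5.3% to 6.6%
- p = 20%: false ratio 1.03 to 1.09 (or its inverse), type I error 5.8% to 9.8%

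The largest shift, 0.083 on the log scale, is about one fifth of 0.405. It assumes that the whole 20% allowance is exposure-related refusal in one arm.

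**Power.** It is about 88% if one charcoal arm alone falls to 24 (normal approximation), and 90.5% with 30 in both arms (t).

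**The case against.** The question is pharmacological: does charcoal, once taken, change the kinetics? Requiring that it was taken fits that question, and the rule is declared in advance with an allowance for ineligible subjects. A matching rule for plain water would serve no evident purpose. One rule for all endpoints is simple, and DHA, which is part of the primary objective, gives the 13 h drink a real role. All of this stands for DHA and for Group 2, whose charcoal is given with the sampled dose. It does not explain why the 13 h drink should decide inclusion for artesunate AUC in Group 3.

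A reader might infer more than the protocol supports:

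- *Control is unfiltered.* It is not. Control is screened for charcoal contamination, and the missed-sample rule covers every arm.
- *The rule will produce a false charcoal effect.* That needs refusal to track artesunate exposure. The protocol gives no such correlation. The deterrents that it names for charcoal are taste and constipation, and Section 2.3 reports no recognised dose-related harm from artemisinin derivatives in humans. Group 2's drinks accompany artesunate, and Group 3's first drink comes 11 h before the sampled dose.
- *The primary analysis should be as-randomised for all endpoints.* That is a trade-off. With a true ratio of 0.67, 10% non-takers give exp(0.9 × ln 0.67) = 0.697 and 20% give 0.726. This dilution would affect artesunate in Group 2 as well as DHA. It is of the same order as the assumed selection bias and pulls towards no interaction.

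**Conclusion.** The point holds in a narrow form. For artesunate endpoints in Group 3, exclusion for missing only the second drink has no pharmacokinetic basis: at least 99.8% of the AUC has accrued when the drink is due, even at the mean plus 3 SD of the stated half-life. This rests on Table 1 and on one-compartment decline. Section 9 also allows a two-compartment fit, and a slow terminal phase would raise the remaining fraction, but the protocol gives no figures that suggest one. Sampling for artesunate formally continues to 6 h, so the curve is complete kinetically rather than by schedule.

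The consequence is lost valid profiles and an avoidable selection after randomisation. The number of subjects affected cannot be known from the protocol. Any bias is of unknown size and probably small against the ratio of 1.5. The sample size is correct and power is not at risk. Section 9 leaves statistical detail to a separate plan, but it fixes this inclusion rule itself. Severity is minor.

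**What to change.** In Section 9, state the completion rule by endpoint:

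- For artesunate endpoints, do not exclude a Group 3 subject solely for missing the second (13 h) charcoal drink.
- For DHA endpoints, keep the requirement that both charcoal drinks were taken.
- For Group 2, keep the charcoal-taken requirement for all endpoints.
- Add a sensitivity analysis, not the primary one, of all subjects with an evaluable profile in the group to which they were randomised.

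The cost is a few sentences and one more run of the same ANOVA, with no new subjects, samples or procedures. The downside is that the artesunate and DHA analysis sets may differ slightly in Group 3, so each table should state its own denominator.
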